### Intervention and control

Twenty sessions will be performed with breathing exercises (spontaneous breathing or using PNF patterns), followed by aerobic exercises for lower or upper limbs, and ending with repetition of the respiratory exercises.

The session will begin with the breathing patterns, with each pattern/exercise being performed 10 times. The therapist will position the hands to perform the maneuvers (Fig. 1). In the control group, the patients will put their hands in the same locations used by the therapist during the PNF (Fig. 2).

The cycling will be performed for 30 min per session. Cycling training will be performed without load with a minimum start speed of 50 rpm following the recommendation of the American College of Sports Medicine for patients with stroke [28]. Participants will be encouraged to increase the number of revolutions per minute throughout the study. Thus, participants will perform the cycling at 50 rpm at the beginning; however, there will not be a minimum number of revolutions per minute to reach by the end of the treatment. The patients will be instructed to develop and maintain their highest speed during the exercise, but they may pause if they feel fatigued or need to slow down.

To perform cardiorespiratory training, individuals must be able to remain safe and stable during cycling, with the paretic limb positioned and tied to the pedal. The volunteers will be monitored every 5 min during the 30 min of exercise on the cycle ergometer to check blood pressure, peripheral oxygen saturation and heart rate. The participants will also be asked about their perception of respiratory effort and fatigue in the limbs at the beginning and end of the activity using the original [29] and modified Borg Scale, respectively.

Three evaluations will be carried out at different times: pretraining, post-training and at 30-day follow-up.

The volunteer can be allocated to one of the following protocols:
Cardiorespiratory training of the lower limbs with respiratory patterns of PNF composed of PNF respiratory exercises patterns, followed by 30 min of exercise on a cycle ergometer carried out by the lower limbs and completed by repeating the PNF exercise breathing patterns.Cardiorespiratory training of the upper limbs with respiratory patterns of PNF composed of PNF respiratory exercise patterns, followed by 30 min of exercise on a cycle ergometer carried out by the upper limbs and completed by repeating the PNF exercise breathing patterns.Cardiorespiratory training of the lower limbs with spontaneous breathing by the individual composed of spontaneous breathing with the hands positioned at the same points where the hands would be positioned by the therapist during PNF patterns, followed by 30 min of exercises on a cycle ergometer performed by the lower limbs and completed by repeating the initial breathing exercises.Cardiorespiratory training of the upper limbs with spontaneous breathing by the individual composed of spontaneous breathing with the hands positioned at the same points where the hands would be positioned by the therapist during PNF patterns, followed by 30 min of exercises on a cycle ergometer performed by the lower limbs and completed by repeating the initial breathing exercises.

During the exercises on the cycle ergometer, the following criteria will be indicated to interrupt the activity:
Systolic pressure above 140 mmHg [31]Diastolic pressure above 100 mmHgPeripheral saturation below 90%At the request of the volunteer for excessive fatigue or pain

### Experimental group

#### Respiratory patterns of PNF

Respiratory patterns of PNF will be performed in different positions:
Supine:
Upper costal: both hands of the therapist are positioned laterally on the first four ribs in the hemiclavicular line, resisting the rib movements during inspiration and assisting the ribs to lower during expiration (Fig. 1a).Sternal: both hands of the therapist are positioned on the sternum, resisting the elevation and anterior movements during the inspiration. In the expiratory phase, the therapist assists the movements in the inferior and posterior direction, reducing the antero-posterior diameter of the trunk (Fig. 1b).Therapist's hands: the therapist’s hand is positioned laterally on the trunk, on the four last ribs, resisting the increase of the lateral diameter of the trunk. During expiration the therapist performs movement in the medial and inferior direction (Fig. 1c).Diaphragmatic: the hands of the therapist are positioned on the lower edges of the 8th/9th ribs in both limbs, resisting the lateral and antero-posterior diameter increases during inspiration and performing medial and inferior movements (Fig. 1d).Right/left lateral decubitus:
Lower costal: both hands of the therapist are positioned on four superposed last ribs (floating), resisting the increase of the lateral diameter of the trunk. The therapist performs movement in medial and inferior directions during expiration (Fig. 1e).Diaphragmatic: both hands of the therapist are positioned overlapping the lower edges of the 8th/9th ribs, resisting increases in lateral and antero-posterior diameters during inspiration and moving in medial and inferior directions (Fig. 1f).Seated position:

**Fig. 1 Fig1:**
[figure not shown]
Proprioceptive Neuromuscular Facilitation patterns in experimental group

**Fig. 2 Fig2:**
[figure not shown]
Proprioceptive Neuromuscular Facilitation patterns in control group

The respiratory patterns in the seated position will follow similar actions proposed for the supine position in the upper costal, sternal and lower costal patterns (Fig. 1g–i).

For the trunk flexion pattern, the hands of the therapist are alternately positioned in the clavicular acromion and scapular spine, creating a support point and resisting trunk flexion and extension movements, respectively. The patient performs a movement of up to 45° of trunk flexion, being instructed to lead the shoulder to the contralateral knee during expiration, rotating the trunk and overcoming the resistance imposed by the therapist. In extension, the individual takes the inspiration and returns to the position of 90°, with resistance in the super-posterior region being guided by the therapist (Fig. 1j and k).

The technique used was stabilization reversal. The patterns are performed in both the most affected and contralateral regions. During PNF application, patients are instructed to breathe in deeply, and they are in control of the onset of inspiratory movement. The therapist will count the respiratory pattern of the patient, and they will be instructed to stop the exercise after 10 respirations have been performed.

#### Measurements

The evaluations will be carried out by a trained researcher who is blinded to the treatment received by the participant. The evaluations will be divided over 2 days to avoid fatigue of the participant. The assessment process will be composed of the Mini-Mental State Examination, anamnesis, plethysmography optoelectronics, manovacuometry, spirometry, a 6-min walk test (6MWT; with inertial walking sensor and gas analyzer), quality of life scale, and Berg balance scale. The database will be populated by the researcher responsible for the evaluation, with the process being performed twice to minimize errors.

#### Primary outcome measures

The primary outcomes are oxygen uptake (VO_2_), balance, quality of life, gait parameters (walking distance, step length, stance and swing time) and rib cage compartment volumes.

Oxygen uptake will be measured during a 6MWT. This test will be performed in a 30-m hallway by a trained therapist following the guidelines proposed by the American Thoracic Society [32]. The 6MWT is validated for patients with stroke [33]; in addition, the VO_2_ obtained in this test presented good validity and reliability with maximum VO_2_ [34]. During the 6MWT participants will be using a telemetry system (MetaMax® 3B, Cortex Biophysik GmbH, Germany) where exhaled gas kinetics (VO_2_, carbon dioxide production (VCO_2_) and the respiratory exchange ratio) will be measured breath-by-breath. The total distance covered and the perception of self-reported effort (Borg Scale, VO_2_, VCO_2_, minute ventilation (VE) and heart rate) will be recorded [32, 35]. The average of the last 30 s of data from the test will be used to determine VO_2peak_, VCO_2_, the respiratory exchange ratio and VE [36].

Balance will be evaluated through the Brazilian version of the Berg Balance Scale (BBS) [37]. BBS evaluates balance based on 14 common activities of daily living items. Each item of the scale presents an alternative of an ordinal scale, varying from 0 to 4 points. The maximum score that can be reached is 56, with a cut-off point of 45 for a risk of falls.

The quality of life evaluation will be evaluated through the stroke-specific quality-of-life scale developed by Williams et al. in 1999 [38] and adapted to the Brazilian population [39]. This is considered a valid measurement scale with adequate reliability (intraclass correlation coefficient, 0.97) for specific evaluation of the quality of life after stroke. It is composed of 49 items distributed in 12 domains. Responses are quantified on a scale that can range from 1 to 5 points and refer to the individual’s performance in the previous 2 weeks. The total score varies from 49 to 245 points, being determined by a greater or lesser dependence and difficulty in performing tasks. The evaluation will be conducted through an interview to avoid a low education level of some participants causing difficulties in answering the questions.

For gait parameters, in addition to collecting expired gases during the 6MWT, the participants will also use the G-walk inertial sensor (BTS Bioengineering, Milan, Italy) to collect the following parameters: walking distance, step length, stance and swing time. The BTS G-SENSOR 2 is a wireless system with an inertial sensor consisting of a three-axis accelerometer, a magnetic sensor and a three-axis gyroscope, which is positioned in L5 for a functional gait analysis. The system calculates all the temporal and spatial gait parameters required to perform a diagnosis or to define a training strategy from the obtained data.

For measurement of the compartmental distribution of the trunk volume volunteers will be referred after an initial evaluation for an analysis of the chest wall kinematics through an optical-electronic plethysmograph (BTS Bioengineering, Milan, Italy) with eight cameras (four anterior and four posterior). According to the protocol of Aliverti and Pedotti [40], 89 reflexive markers will be fixed with hypoallergenic bioadhesive on the anterolateral and posterior faces of the trunk in a grid system. Volunteers will be seated with their feet flat on the floor, knees and hips at 90°, with an erect spine with hands resting on their hips, and then asked to perform quiet breathing without speaking and without changing their posture during the image acquisition.

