**Methods/design:**

A blind, randomized clinical trial with allocation confidentiality will be performed. Forty patients will be randomized into four groups: CRT-lower limb (LL) plus PNF; CRT-LL and respiration; CRT-upper limb (UL) plus PNF; or CRT-UL and respiration. Individuals will be evaluated at three different times (pretreatment, after 20 days of treatment and 1 month after the end of treatment). The treatment protocol consists of respiratory exercises, 30 min of CRT (cycle ergometer) and then repetition of the respiratory exercises, performed three times a week over a period of 20 days. Primary outcome measures are quality of life, gait, balance, peak oxygen uptake and rib cage compartment volumes. As secondary outcomes, respiratory function and maximal inspiratory and expiratory pressures will be measured.

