### Sample size calculation

The sample size was calculated using the G*Power Program (Version 3.1.9.2, University of Kiel, Germany) and the variable VO_2peak_ (in liters per minute) was adopted as the primary outcome measure. According to a previous study involving individuals with poststroke hemiparesis who performed cycling training [48], standard deviations observed in the experimental and control groups were 0.16 and 0.13, respectively. The sample size was calculated from these data to detect a difference in VO_2peak_ between the groups after intervention of 0.24 l/min (α = 5% and power = 80%), using a two-sample *t* test for mean difference. The sample required was eight patients; considering a follow-up loss of 20%, 10 individuals will be allocated into each intervention group: 10 individuals in the experimental lower limb group (cardiorespiratory training of the lower limbs plus PNF), 10 individuals in the control lower limb group (cardiorespiratory training of the lower limbs plus breathing), 10 individuals in the experimental upper limb group (cardiorespiratory training of the upper limbs plus PNF) and 10 individuals in the control upper limb group (cardiorespiratory training of the upper limbs plus breathing).

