### Statistical analyses

A descriptive analysis of the data will be initially performed. Frequency distribution will be obtained for the categorical variables, and central tendency and dispersion measures will be obtained for the numerical variables. The Kolmogorov-Smirnov/Shapiro-Wilk test and the Levene test will be used to evaluate the normality of the variables and the homogeneity of the sample, respectively.

All tests will be applied assuming a 95% confidence level, considering a significant *P* value <0.05. An intention-to-treat analysis will be performed in case of patient withdrawal or interruption of training, using the last observation carried forward. Two-way repeated-measures analysis of variance to determine the interaction intervention by time (pretraining, post-training and 30 days of follow up) for the outcome variables will be conducted for the experimental and control lower limb interventions and the experimental and control upper limb interventions separately. Paired *t* tests will be used to compare clinical outcomes between preintervention and post-training for experimental and control groups. Independent *t* tests will be also used to separately compare upper limb experimental and control groups and lower limb experimental and control groups post-training.

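### Five unranked primary outcome domains are each tested at an unadjusted 5% in two limb pairs, while the sample size rests on VO2peak alone

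*Protocol article*

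**What the plan says.** The protocol article names its primary outcomes in three places.

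- Abstract, Methods/design: "Primary outcome measures are quality of life, gait, balance, peak oxygen uptake and rib cage compartment volumes".
- Primary outcome measures, in the body of the article: "The primary outcomes are oxygen uptake (VO_2_), balance, quality of life, gait parameters (walking distance, step length, stance and swing time". The list closes with the volumes of the rib cage compartments. Gait alone contributes four named variables, so the list holds at least eight. No order of importance is given.
- Sample size calculation: "the variable VO_2peak_ (in liters per minute) was adopted as the primary outcome measure". The calculation uses a two-sample t test for a difference of 0.24 l/min, SDs of 0.16 and 0.13, α of 5% and power of 80%. It arrives at 8 per group, raised to 10 for 20% loss.

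The Statistical analyses section sets one threshold for everything: "All tests will be applied assuming a 95% confidence level, considering a significant *P* value <0.05". The repeated-measures analysis is run "for the experimental and control lower limb interventions and the experimental and control upper limb interventions separately". The same section adds independent t tests of experimental against control at post-training, again by limb. Each outcome therefore has two between-group tests in each limb pair, and neither is named as the deciding one.

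**The concern.** A reader cannot tell from the article which result answers the trial's question. Five domains carry equal primary status, each is compared in two pairs of groups, and each comparison uses the full 5%. Under such a plan, one nominally significant result among ten or more can appear by chance and still rank as a primary finding.

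Only VO2peak has a power justification. For balance, quality of life, gait and rib cage volumes the article gives no target difference and no variance, so a null result on them cannot be interpreted either. With 10 patients per group, the main conclusion could rest on whichever domain happened to cross the threshold.

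This does not depend on detail that an unseen analysis plan might supply. The article itself fixes both the list of primary outcomes and the threshold for all tests.

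**Working it through.** **Inputs.** Five domains, or eight named variables counting rib cage volumes as one (Primary outcome measures). Two limb pairs and 0.05 per test (Statistical analyses). SDs 0.16 and 0.13, difference 0.24 l/min, 8 and then 10 per group (Sample size calculation). Assumed, because not stated: two-sided testing, and the correlations between outcomes.

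**Step 1: the plan's own sample size.** Pooled SD = √[(0.16² + 0.13²)/2] = 0.1458, so d = 0.24/0.1458 = 1.646. The exact two-sided t test has power 80.7% with 7 per group and 86.4% with 8. Using 0.16 for both groups (d = 1.5), 8 per group gives 79.7%. Allowing for loss, 8/0.80 = 10. The stated 8 and 10 are reproduced closely enough. They cover one unadjusted VO2peak comparison within one limb pair.

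**Step 2: chance of at least one false positive, independent tests, no true effects.** The formula is 1 − 0.95^k.

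| Family | k | Probability |
|---|---|---|
| VO2peak only, both pairs | 2 | 9.75% |
| Five domains, one pair | 5 | 22.6% |
| Five domains, both pairs | 10 | 40.1% |
| Eight variables, both pairs | 16 | 56.0% |

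**Step 3: allowing for correlation.** The two limb pairs contain different patients, so they are independent of each other. Outcomes within a pair are measured on the same patients and are not. I simulated post-training t tests with 10 per group, equal correlation r between outcomes within a pair, independent pairs and no true effects.

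| r | Five domains × 2 | Eight variables × 2 |
|---|---|---|
| 0.3 | 38% | 52% |
| 0.5 | 33% | 45% |
| 0.7 | 29% | 36% |
| 0.9 | 20% | 24% |

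These figures count one between-group test per outcome and pair. The plan has two (the group-by-time interaction and the post-training t test), which raises every entry by an amount that depends on how closely the two agree.

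**Step 4: VO2peak power under stricter thresholds** (d = 1.646, two-sided).

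| Alpha per test | 8 per group | 9 per group | 10 per group |
|---|---|---|---|
| 0.05 | 86.4% | 90.6% | 93.6% |
| 0.025 (two pairs) | 77.3% | 83.4% | 88.0% |
| 0.005 (Bonferroni, ten tests) | 51.1% | 60.1% | 68.1% |

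At 0.005, 80% power needs 12 evaluable per group. That is 12/0.80 = 15 enrolled per group, or 60 in total against the planned 40.

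**The case against.** Four objections deserve an answer.

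*The 40% is a special case.* This stands. It needs ten independent tests and no true effect anywhere. Independence within a pair is implausible, since VO2 and the gait variables all come from the same six-minute walk. A reader might infer that the plan simply carries a 40% false-positive risk; the documents do not support that, because they give no correlations. In the other direction, 40% is not a ceiling either: it counts gait once and leaves out the second between-group test.

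*The two limb pairs may be two questions.* This is a fair reading. They involve different patients and different training, and are analysed separately. The independence figure is then 22.6% per pair. Treating them as one family is also defensible, because the Discussion states a single purpose: the efficacy of adding PNF patterns to cardiorespiratory training. The plan should say which applies.

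*The sections need not contradict each other.* A reader might infer that the sample size section declares VO2peak the sole primary outcome. Its wording, "was adopted as the primary outcome measure", can equally mean that one of several primary outcomes was picked for sizing, and it does not demote the other four. What stands is narrower: there are several primary outcomes, no ranking or success rule, and power for only one.

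*Adjustment could rescue the present list.* Partly. A reader might infer that any correction ruins the trial. The 51% is Bonferroni, a severe choice, with 8 per group; with 10 it is 68%. A fixed sequence starting with VO2peak would test it at full alpha within a pair. But no such procedure is in the plan, and none would give the other four domains a power justification.

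**Conclusion.** The point holds in a bounded form. As written, the plan has at least ten primary between-group comparisons at 5% each, no ranking, and a sample size that covers one of the five domains. With no true effects, the chance of at least one false-positive primary result is about 40% under independence and about 20% to 38% for assumed within-pair correlations of 0.9 down to 0.3. Even the lowest of these is four times the nominal 5%. Counting the eight named variables gives 24% to 56% over correlations from 0.9 to zero.

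The sample size calculation itself is not in error. Nor does the article say that a single significant domain would be declared a positive trial. It states no success rule at all, and that absence is the weakness.

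**What to change.** 1. In the Abstract and in Primary outcome measures, name VO2peak at the post-training assessment as the single primary outcome. This is consistent with the sizing. Move balance, quality of life, gait and rib cage volumes to secondary, reported with estimates and 95% confidence intervals and no confirmatory claim, or else Holm-adjusted.
2. In Statistical analyses, name one between-group test as decisive for VO2peak: either the group-by-time interaction or the post-training comparison, not both.
3. In the same section, state how alpha is handled across the two limb pairs. Either use 0.025 each (or Holm), or declare the pairs two separate questions and acknowledge the joint error of 1 − 0.95² = 9.75%. Making VO2peak the sole primary outcome does not settle this by itself.
4. Restate the power. At 0.025 per pair, 8 evaluable per group gives 77%, below the stated 80%; 9 gives 83% and 10 gives 88%.

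The cost is that four domains lose primary status and the registry entry, which was not available for this review, probably needs a dated update. Recruitment was under way when the article was written, so this is a change during the trial; it should be recorded as such and made before any unblinded analysis. No further patients are needed if the lower power at 8 per group is accepted and stated. Keeping all five domains as primary would instead need a stated multiplicity procedure and a new sample size.

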#### Secondary outcome measures

Respiratory function will be assessed using a Koko spirometer with which the following variables will be measured: inspiratory capacity, forced expiratory volume in 1 s (FEV1), forced vital capacity (FVC), FEV1/FVC, and peak expiratory flow. Spirometry will be performed with the participants in a seated position, with feet resting on the floor, an erect spine, without restraints on the upper limbs and using a mouthpiece and nasal clip. At least three FVC and slow vital capacity maneuvers will be performed, with a 2-min interval between maneuvers according to the American Thoracic Society reproducibility and acceptability criteria [41] and the guidelines for function testing [42], in which a variation of 0.2 l between the tests and the average of the three measurements will be considered [43]. The spirometric values will be expressed as the percentage of the predicted normal value for the Brazilian population [44].

An MV-330 model manovacuometer (Marshal Town Instrumentation Industries, USA) will be used to measure maximal inspiratory and expiratory pressures. The participants will be in a seated position, with feet supported on the floor, an upright spine, without support for the upper limbs and using a mouthpiece and nasal clip, and will be instructed to perform a maximum and sustained inspiration to measure the maximal inspiratory pressure from the residual volume, and perform a maximum expiration to measure the maximal expiratory pressure from the total lung capacity [45]. The best among three maneuvers will be used to record the data.

The oxygen uptake efficiency slope (OUES) represents a relationship between VO_2_ and VE. It is a logarithm of the ventilatory equivalent of oxygen. The OUES can be obtained using the equation (VO_2_ = *a* log VE + *b*). In this equation, the constant *a* represents the regression coefficient (called the OUES), and *b* represents the intercept. OUES correlates with maximum VO_2_ and can predict respiratory capacity during exercise as well as exercise tolerance in patients with various pathologies without the need for maximum effort [46, 47].

